### Statistical analysis

Between-group differences will be calculated, accounting for baseline scores, for all three groups on all outcomes. To address the primary aim, unstructured linear mixed regression will be used to test for group differences on the primary outcomes, with group allocation (COMP-MST, COMP, waitlist control) as the between-subject factor, and time (baseline, post intervention, 3-month follow-up) as the within-subject or repeated variable. Any demographic or neuropsychological variables that are significantly associated with the primary outcome and unevenly distributed between the groups will be included as covariates. The same approach will be used with secondary outcome variables to address the secondary aim. Missing data will be handled using an intention-to-treat analysis (i.e., most recent available data will be imputed). Using planned comparisons, data from the 6-month follow-up will be compared with post-intervention and/or 3-month follow-up results to evaluate whether or not any significant gains on variables have been maintained over time.

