### Procedure

#### Randomization

Participants’ impairment of PM function as assessed on the CAMPROMPT (“impaired/borderline” or “less impairment”) will be used to determine their stratification subgroup for random allocation to the three groups. This stratified approach is designed to ensure a relatively equal proportion of individuals in each group with severe PM impairment, as determined using cutoffs in the CAMPROMPT manual [36]. The random assignment will be conducted independent of the project staff involved in the interventions and the blind assessor. For each subgroup (i.e., severe or less severe), participants will be randomly allocated to COMP, COMP-MST, or waitlist control groups using sequentially numbered and sealed opaque envelopes. The envelopes will contain group allocation on a written insert, based on a predetermined, random, computer-generated sequence.

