#### Secondary outcomes

The Cambridge Prospective Memory Test (CAMPROMPT; [36]) is a psychometric test of PM function. The CAMPROMPT consists of a total of six PM tasks, three cued by time and three cued by events. Participants are allowed to spontaneously use strategies, such as taking notes, to help them remember during tasks. Total scores are out of 36 (time-based and event-based subscale scores are each out of 18), with higher scores representing better PM performance. The validity and reliability of the CAMPROMPT has been documented in a number of studies [36, 41]. In addition to total CAMPROMPT scores, participants’ spontaneous use of note-taking as a PM strategy during the CAMPROMPT will be measured as a dichotomous variable.

The Awareness Questionnaire (AQ; [42]) is a 17-item scale that assesses self-awareness of brain injury-related impairments across sensory, physical, cognitive, and behavioral domains. Ratings on the AQ compare participants’ post-injury abilities on each item to their preinjury functioning (1 = much worse, 5 = much better). The AQ has two versions, a self-report and a significant-other report which may be completed by a family member, friend, or therapist. Positive discrepancy scores (self-report minus significant-other report) indicate impaired self-awareness. The AQ has been found to have sound psychometric properties [43] and has demonstrated sensitivity to change in the context of awareness interventions [35].

Self-awareness specifically for PM impairment will be measured using the BAPM by calculating the discrepancy between participant self-ratings and significant other ratings of the frequency of PM failure in everyday life.

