### Sample size

To determine the required sample size, a power calculation was conducted using the primary outcome variable with the most conservative effect size from our previous RCT (i.e., the change score between pre-and post-SPRS-2 scores) [9]. Comparison between the group that received compensatory plus self-awareness training and the group that received compensatory training alone produced an effect size of 0.70 (Cohen’s *d*). Using G*Power [46] and setting the effect size to 0.70, alpha level to 0.05, and power to 0.80 it was calculated that a sample size of *n* = 26 for each group is required. The sample size has been inflated to *n* = 30 per group to allow for an estimated dropout rate of approximately 10% based on dropout rates from another RCT currently being conducted within the same setting [47]. Therefore, it is calculated that a total sample size of *n* = 90 will be required for the study to be adequately powered to detect significant differences between groups.

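### Covariates for the primary model are chosen by observed significance and imbalance, a rule that will seldom admit the CAMPROMPT stratum and gives up some precision; fix them in advance and state one use of baseline

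*Protocol article*

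**What the plan says.** All references are to the protocol article.

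- **Statistical analysis, covariates:** "Any demographic or neuropsychological variables that are significantly associated with the primary outcome and unevenly distributed between the groups will be included as covariates". Both conditions must hold. The section sets no threshold for unevenness, and it carries the same approach over to the secondary outcomes.
- **Statistical analysis, model:** a linear mixed regression with group as the between-subject factor and "time (baseline, post intervention, 3-month follow-up) as the within-subject or repeated variable". The section opens with "Between-group differences will be calculated, accounting for baseline scores, for all three groups on all outcomes".
- **Randomization:** CAMPROMPT impairment, in two levels, "will be used to determine their stratification subgroup for random allocation to the three groups". The purpose is given as "This stratified approach is designed to ensure a relatively equal proportion of individuals in each group with severe PM impairment". Allocation within each subgroup is "based on a predetermined, random, computer-generated sequence"; blocking is not mentioned.
- **Primary outcomes:** there are two, the BAPM and the SPRS-2, both rated by the significant other. The covariate rule speaks of the primary outcome in the singular.

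**The concern.** A covariate earns its place in a randomized comparison by being prognostic, which is best judged before the data are seen. This rule decides after the event, from the association with outcome and the imbalance in this sample.

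The imbalance condition also works against the design. A factor chosen for stratification because it is thought to matter is balanced on purpose, and then fails the test for entering the model because it is balanced. Selection is tied to the outcome, so the BAPM and SPRS-2 analyses may adjust for different variables.

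The text on baseline adds a second uncertainty. Between-group differences are to account for baseline, yet baseline is also one of the three levels of the repeated factor. The reader cannot tell whether the effect is a contrast of changes or a baseline-adjusted difference. At stake is precision in a trial of 30 per group, not the validity of a positive result.

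**Working it through.** **1. The plan's own figure.** Sample size gives "setting the effect size to 0.70, alpha level to 0.05, and power to 0.80" and 26 per group. A two-sample noncentral t calculation returns 26 with one-sided alpha 0.05 (power 0.801). Two-sided, 34 are needed and 26 give power 0.697. Sidedness is not stated; that is a separate matter, but it shows there is little power to spare. With 30 per group and about 10% dropout, 30 × 0.9 = 27 per arm remain. The steps below use 27 per arm, two-sided 0.05 and d = 0.70.

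**2. Would the stratum meet the rule?** The rule was simulated with two arms, 4,000 runs per scenario and blocking within strata (assumed). There were five further covariates, each explaining 5% of variance, and p < 0.05 was used for both conditions. The stratum was selected in 0 of 4,000 runs in every scenario. At least one covariate of any kind was selected in about 9% of runs.

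**3. Cost of omitting the stratum in a single-visit comparison.** Let R² be the share of outcome variance that the stratum explains (assumed; the document gives none), f = √(1 − R²) and θ = 0.70/√(2/27) = 2.572. By normal approximation:

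- power without the stratum = Φ((θ − 1.96)/f)
- power with the stratum = Φ(θ/f − 1.96)

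| R² | Reported SE too large by | Power without | Power with |
|---|---|---|---|
| 2% | 1.0% | 0.732 | 0.738 |
| 5% | 2.6% | 0.735 | 0.751 |
| 10% | 5.4% | 0.741 | 0.774 |
| 20% | 11.8% | 0.753 | 0.820 |

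The loss is about 1 to 3 points for R² of 2% to 10%, and about 7 points at 20%.

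**4. The same question for a change contrast.** If the stratum shifts a person's score by the same amount b at every visit, then post minus baseline contains b − b = 0. Adding the stratum as a main effect then changes neither the contrast nor its standard error. The loss in step 3 arises only if the stratum predicts change, or if baseline is a covariate and the stratum adds to it.

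**5. Behaviour of the rule as a whole** (the simulation of step 2, single visit):

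| Analysis | Power, stratum 5% | Power, stratum 15% |
|---|---|---|
| Plan's rule | 0.702 | 0.712 |
| No covariates | 0.715 | 0.727 |
| Stratum only | 0.732 | 0.775 |
| Stratum and all five, prespecified | 0.811 | 0.865 |

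Type I error under the rule was 0.045 and 0.029. With a looser threshold for unevenness (p < 0.20, stratum 5%) it was 0.035. The rule gained nothing over an unadjusted analysis and erred on the conservative side. The last row depends on the assumed five useful covariates.

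**6. Baseline handling.** With equal variances σ² and pre-post correlation r (assumed), a change score has variance 2σ²(1 − r) and a baseline-adjusted score has σ²(1 − r²). The ratio is (1 + r)/2.

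- r = 0.8: ratio 0.90, a 10% cut. Effective d = 0.70/√0.90 = 0.738.
- r = 0.5: ratio 0.75, a 25% cut. Effective d = 0.70/√0.75 = 0.808.

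The planned d is itself on the change-score scale. By noncentral t at 27 per arm, power goes from 0.714 to 0.758 (r = 0.8) or 0.830 (r = 0.5).

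**The case against.** The strongest reply is that an article leaves full model terms to the complete protocol or the SAP, so silence on a stratum term is not exclusion. That is fair for the stratum term and for the named contrast. It does not cover the covariate rule, which the article states outright: an SAP that follows it inherits the weakness, and one that does not will contradict it.

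Several stronger readings are tempting, and the document does not support them.

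- **The rule bars CAMPROMPT.** It does not do so by name. The instrument "is a psychometric test of PM function" and could count as a neuropsychological variable. Blocking is not stated, and without it the stratum could turn out uneven and qualify. Exclusion is likely, not certain.
- **Data-driven selection inflates false positives.** The simulations show the opposite. Nor does a long candidate list make spurious selection likely, because both conditions must hold: for 12 independent noise candidates at 5% each, 1 − (1 − 0.05²)^12 is about 0.03.
- **Baseline is used twice, or the effect is averaged over a visit with no treatment difference.** The article does not say that baseline is also entered as a covariate, or that the test is a group main effect over three visits. Accounting for baseline may simply describe the mixed model. The hypotheses, improvement at post intervention and maintenance at 3 months, fit group-by-time contrasts.
- **Omitting the stratum is costly.** The primary outcomes are significant-other questionnaires and the stratum is a dichotomized test. The Background reports that the gains seen on CAMPROMPT in the earlier trial did not extend to significantly greater gains in everyday memory or psychosocial function. A large R² cannot be presumed.

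**Conclusion.** The concern stands as a modest, inexpensive improvement. The plan fixes a covariate rule that depends on the trial's own data, will seldom admit the factor used for stratification, and may give the two primary outcomes different models. Its effect is conservative: it forgoes precision and does not threaten a positive finding.

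Omitting the stratum alone costs about 1 to 3 power points for an assumed 2% to 10% of variance, and about nothing for a change contrast if the stratum effect is constant over time. The baseline wording is ambiguous rather than wrong. If it means free group means at baseline, the group-by-time contrast is a change-score analysis, and baseline adjustment would cut its variance by 10% to 25% for r from 0.8 to 0.5. That gain does not arise if the trial already intends baseline adjustment. Neither the variance shares nor the correlation is in the document.

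**What to change.** Replace the selection rule with one fixed model for each primary outcome:

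- **Responses:** the post-intervention and 3-month scores.
- **Fixed effects:** group, visit, group × visit, the baseline value of that outcome, and CAMPROMPT stratum. Equivalently for baseline, keep it as a response with a common mean constrained across groups.
- **Covariance:** unstructured, as already planned.
- **Effect:** the group contrast at a named visit.
- **Further covariates:** named in advance and kept whatever their observed significance or imbalance.

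The cost is wording and one or two degrees of freedom. Every variable is already collected.

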### Study objectives and hypotheses

The primary aim of this RCT is to evaluate the effectiveness of a MST approach to compensatory PM training for improving everyday PM performance, maintaining PM gains, and improving level of psychosocial reintegration in community-dwelling adults with moderate to severe TBI. The secondary aim is to evaluate the effectiveness of a MST approach to compensatory PM training for improving and maintaining PM function on psychometric testing, strategy use, self-awareness, and level of care following TBI.

It is proposed that, with the addition of MST to the compensatory program, individuals with TBI will become aware of the extent of their PM failures, and the gains in PM performance will extend to everyday life as the participants will be able to generalize their strategy use to situations beyond the training setting. Therefore, it is hypothesized that:COMP training will demonstrate significant improvement at post intervention and maintenance at 3-months post intervention on PM performance and level of psychosocial integration compared to no intervention (i.e., waitlist), and that compensatory PM rehabilitation combined with metacognitive skills training (COMP-MST) will be more effective than COMP training aloneCompared to participants in the waitlist condition, participants who receive COMP training will demonstrate significant improvement and maintenance of PM function on psychometric testing, strategy use, self-awareness, and level of support needs and, furthermore, that COMP-MST training will be more effective than COMP training alone

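### Filling missing visits with the last value, labelled intention-to-treat, pulls later change toward zero and makes the estimates look more precise than the observed data allow

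*Protocol article*

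**What the plan says.** The Statistical analysis section plans that "unstructured linear mixed regression will be used to test for group differences on the primary outcomes", with "time (baseline, post intervention, 3-month follow-up) as the within-subject or repeated variable". Secondary outcomes follow: "The same approach will be used with secondary outcome variables to address the secondary aim". Missing data get one sentence: "Missing data will be handled using an intention-to-treat analysis (i.e., most recent available data will be imputed". For maintenance, "data from the 6-month follow-up will be compared with post-intervention and/or 3-month follow-up results".

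Under Study objectives and hypotheses, maintenance belongs to the primary aim, which covers "improving everyday PM performance, maintaining PM gains, and improving level of psychosocial reintegration". The first hypothesis includes "maintenance at 3-months post intervention on PM performance and level of psychosocial integration", each relative to waitlist. The Sample size section expects about 10% dropout. It does not say when people are expected to leave.

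**The concern.** There are three difficulties.

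1. **The label is wrong.** Intention-to-treat settles which participants are analysed and in which arm. Replacing a missing score with an earlier one is a separate assumption, and it needs its own justification.
2. **The rule overrides the model.** A likelihood-based mixed model with unstructured covariance keeps people with incomplete follow-up by using the visits they have. Baseline is a level of the time factor and is measured before randomisation (Trial design), so every randomised participant with a baseline score contributes without imputation. The article does not spell out the order of steps, but filling visits that the model uses implies imputing first and then fitting to the filled values as if they were observed.
3. **The rule partly presupposes the answer on maintenance.** A person lost after an earlier visit enters the later comparison with no change at all.

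At stake are the size and apparent precision of the 3-month group effects and of the 6-month maintenance comparisons. Gaps are realistic. Both primary outcomes are rated by the significant other, who may return the forms by post (Data collection and management), so a primary score can be missing even when the participant attends.

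**Working it through.** **Inputs from the article.** d = 0.70 on the pre-post change in SPRS-2; 26 per group, raised to 30; about 10% dropout; visits at baseline, post-intervention, 3 and 6 months.

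**Inputs assumed.** The article does not give the within-person correlation, the amount of decay or the timing of dropout. Ranges are shown.

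**The plan's own figure.** 26/0.9 = 28.9, so 29, close to the stated 30. In reverse, 30 × 0.9 = 27 observed per arm, which covers 26. Dropping the imputation rule therefore does not change the planned sample size. (The 26 itself is reproduced only with a one-sided 0.05; two-sided gives 34. That is a separate matter.)

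**Within-arm change after the post visit.** Let m be the fraction imputed, L the true loss, r the correlation and n = 30.

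- Loss after carry-forward: (1 − m)L.
- Its SE: √{[(1 − m)·2(1 − r) + m(1 − m)L²]/n}.
- SE from observed pairs: √{2(1 − r)/[n(1 − m)]}.

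With L = 0.35 SD and r = 0.7, 2(1 − r) = 0.6. At m = 0.10 the carry-forward SE is √[(0.54 + 0.09 × 0.1225)/30] = 0.136, and the observed-pairs SE is √(0.6/27) = 0.149.

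| m | Loss, carried forward | SE | Ratio | Loss, observed | SE | Ratio |
|---|---|---|---|---|---|---|
| 10% | 0.315 | 0.136 | 2.32 | 0.35 | 0.149 | 2.35 |
| 20% | 0.280 | 0.129 | 2.17 | 0.35 | 0.158 | 2.21 |
| 30% | 0.245 | 0.122 | 2.01 | 0.35 | 0.169 | 2.07 |

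(Ratio is loss divided by SE, from unrounded values.) Under carry-forward the SE falls as more data are lost; it should rise. At 20%, approximate 95% intervals for the loss are 0.28 ± 1.96 × 0.129 = 0.03 to 0.53, against 0.35 ± 1.96 × 0.158 = 0.04 to 0.66. The lower limit hardly moves, but the largest loss compatible with the data drops.

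**Between-group effect at 3 months.** Suppose one arm gains g, keeps g/2, and the comparator does not change. If all dropouts leave after the post visit, carry-forward gives (1 − m)g/2 + mg = (1 + m)g/2. If all leave before it, carry-forward gives (1 − m)g/2. With r = 0.6, g = 0.70 × √0.8 = 0.626, so the true effect is 0.313. At 10% the results are 0.344 or 0.282, a bias of ±0.031. With r = 0.5 between baseline and follow-up, g = 0.70 and the bias is ±0.035.

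**Unequal dropout, no true group difference.** Let both arms gain 0.8 SD and keep 0.4, with 5% versus 20% dropout. The bias is (0.20 − 0.05) × 0.4 = 0.06 SD, positive or negative depending on timing.

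**Simulation.** Two arms of 30, three visits, dropout completely at random, 1,500 replicates per scenario; correlations 0.6 throughout, or 0.7 adjacent and 0.5 two visits apart.

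- True 3-month effect 0.313: at 10% dropout, carry-forward gave 0.351 (late leavers) or 0.278 (early leavers); at 20%, 0.373 or 0.258.
- True post-to-3-month change −0.313, 20% late dropout: carry-forward −0.247; mixed model without imputation −0.306.
- Carry-forward SE divided by the sampling SD of the mixed-model estimate, within arm: 0.87–0.93 at 10%, 0.77–0.84 at 20%.
- The same ratio between groups: 0.88–0.98 at 10%, 0.80–0.93 at 20%.
- Between-group type I error with equal dropout: near 5%.

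**The case against.** The strongest reply is that at the planned dropout little changes in the tests, and much of this stands.

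- **Test of decline.** The estimate and its SE shrink together. In the scenario above, simulated power to detect the loss was 0.616 with carry-forward and 0.618 without at 10% missing, and 0.498 versus 0.502 at 30%. The rule barely alters the chance of detecting a true decline.
- **Between-group test.** With equal random dropout the false-positive rate is preserved. The carry-forward SE is close to the actual spread of the carry-forward estimate; it is too small only relative to the information in the observed data.
- **Timing.** A reader might infer that all dropouts are credited with maintained gains. That is true only of those lost after the post-intervention visit. Those lost earlier are credited with no gain, and an even mix of the two nearly cancels the 3-month between-group bias.
- **Effect size.** A reader might also infer that d falls from 0.70 to 0.70 × 0.9 = 0.63. That figure is a mean difference in original SD units with every dropout leaving before the post visit. The added zeros also reduce the spread. With a flat comparator the pooled variance is (0.9 + 0.09 × 0.49 + 0.9)/2 = 0.922, so d = 0.63/0.960 = 0.66. If the comparator improves by 0.5 SD, d is about 0.64.
- **Sensitivity analysis.** Its absence is not a fault here, since that is commonly left to the statistical analysis plan.

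What remains is that the article states the rule outright, the rule biases the estimates, and it discards what the chosen model does well.

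**Conclusion.** The point holds as a badly chosen missing-data rule under a wrong label. Change after the last observed visit is pulled toward zero by about the fraction imputed: 10% at the planned dropout, 20% at twice that. The 3-month between-group effect can be overstated or understated, by about 0.03 to 0.04 SD at 10% dropout when half the gain fades, and by about 0.06 SD with 5% versus 20% dropout and no true difference. The rule is therefore not dependably conservative. Standard errors are about 0.87 to 0.98 of the supported value at 10% dropout.

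These sizes rest on assumed correlation, decay and timing, and on random dropout. If gains are fully kept, the imputed zeros are right on average and only the false precision remains. The documents do not support a claim that the primary between-group test is invalid. The harm is to estimates and intervals: modest at 10% dropout, larger if dropout is higher or differs by arm.

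**What to change.** Replace the missing-data sentence in the Statistical analysis section with a statement along these lines: all randomised participants are analysed in the group to which they were allocated; the mixed model is fitted by likelihood to all observed visits, without imputation, assuming data are missing at random. Make the 6-month maintenance comparisons as contrasts from the same kind of model with the 6-month visit included, so that they too use observed data. Apply this to the secondary outcomes wherever the same approach is used. A sensitivity analysis allowing for data missing not at random is optional and can be left to the statistical analysis plan.

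The cost is one or two sentences, with no new data and no change to the planned 30 per group. The change should be made before the data are analysed by group.

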## Methods/design

### Trial design

The research design entails a RCT with three treatment groups: COMP-MST, COMP, and waitlist control. After completing baseline assessment measures (see “Measures” section), participants will be randomly allocated to the COMP-MST, COMP, or waitlist control group (see “Randomization” section). The COMP-MST and COMP groups will participate in a 6-week treatment intervention (see “Intervention procedures” section), and the waitlist control group will receive usual care for 6 weeks. At the end of the 6-week period, all participants will be reassessed on measures used at baseline by a blind assessor. Three months after conclusion of the intervention programs and waitlist control condition, all participants will receive a follow-up assessment to evaluate the maintenance of treatment effects. At this time, participants in the waitlist group will be offered the COMP-MST program. Six months after completing the intervention programs, all treatment groups will receive further follow-up assessment to determine maintenance of gains. The trial design flowchart is listed in Fig. 1 and the Standard Protocol Items: Recommendations for Interventional Trials (SPIRIT) diagram in Fig. 2.

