### Measures

The primary outcome measures assess everyday PM performance and level of psychosocial reintegration. Secondary outcome measures assess PM performance and strategy use, global self-awareness, self-awareness of PM failure, and level of support needs. Primary and secondary outcome measures will be administered at pre and post intervention, and at 3-month and 6-month follow-ups.

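### The 6-month maintenance question is answered only by comparison over time on variables already found significant, and the randomised COMP-MST versus COMP difference at 6 months is not planned

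*Protocol article*

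**What the plan says.** All groups are measured at 6 months. The Measures section states: "Primary and secondary outcome measures will be administered at pre and post intervention, and at 3-month and 6-month follow-ups". Trial design gives the purpose: "Six months after completing the intervention programs, all treatment groups will receive further follow-up assessment to determine maintenance of gains".

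The Statistical analysis section sets out a linear mixed model for group differences, with "time (baseline, post intervention, 3-month follow-up) as the within-subject or repeated variable". Six months is not a level of that factor. The 6-month data appear only in the last sentence of the section, where by planned comparison "data from the 6-month follow-up will be compared with post-intervention and/or 3-month follow-up results to evaluate whether or not any significant gains" have persisted.

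Three other statements bear on this:

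- The section opens with "Between-group differences will be calculated, accounting for baseline scores, for all three groups on all outcomes", which names no time point.
- Missing values are replaced: "most recent available data will be imputed".
- Trial design says of the 3-month visit: "At this time, participants in the waitlist group will be offered the COMP-MST program".

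**The concern.** Four features of the 6-month analysis work against a clear answer.

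1. It looks for a difference from an earlier visit in order to support a claim of no important difference. Without a margin or a confidence-interval criterion, the only result that could favour maintenance is a failure to find decline.
2. It is confined to variables whose gain was already significant. Such variables tend to have an overstated reference value, so some later decline is expected from selection alone.
3. The reference visit is open (*and/or*), so it could be chosen after the data are seen.
4. Nothing in the section asks whether COMP-MST is better than COMP at 6 months. Both arms are assessed then, and only the waitlist arm is offered a change of treatment.

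Maintaining gains is part of the primary aim, and the trial is sized on the comparison of compensatory training with and without the awareness component. As written, the plan would report on long-term durability without a randomised estimate of it.

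**Working it through.** **The plan's own figure.** The Sample size section gives 26 per group for d = 0.70, alpha 0.05 and power 0.80, raised to 30 for about 10% dropout. The noncentral-t two-sample test reproduces 26 if one-sided (power 0.801); two-sided, 26 per group gives 0.70. Sidedness is not stated. The calculation concerns a between-group difference in pre-post SPRS-2 change. Nothing in the document sizes the 6-month comparison.

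**Inputs for the illustration.**

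- Completers per arm: 30 × 0.9 = 27 (Sample size section).
- Within-arm loss between the reference visit and 6 months: 0.35 SD. This is an assumption, set at half of 0.70. The 0.70 is a between-group figure and is borrowed only as a scale.
- Between-visit correlation r: 0.5, 0.7 or 0.8, an assumption.
- Two-sided paired t test at 0.05 within one arm, also an assumption, since the contrast is not specified.

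**Formula.** The SD of the paired difference is √(2(1 − r)), so the standardised loss is dz = 0.35/√(2(1 − r)). The noncentrality is dz × √27, on 26 degrees of freedom, with critical value 2.056.

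| r | dz | Noncentrality | Power | Loss missed |
|---|---|---|---|---|
| 0.5 | 0.350 | 1.82 | 0.42 | 58% |
| 0.7 | 0.452 | 2.35 | 0.62 | 38% |
| 0.8 | 0.553 | 2.88 | 0.79 | 21% |

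**Sensitivity to the assumed loss and to pooling.**

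- Loss of 0.175 SD: power 0.14 to 0.28 over the same correlations.
- Loss of 0.50 SD (half of an assumed 1.0 SD gain), r = 0.5: power 0.71.
- Loss of 0.70 SD: power 0.94 or more.
- Loss of 0.35 SD with the two trained arms pooled (27 + 27 = 54), r = 0.5: power 0.71.

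**What showing maintenance would take.** Take an illustrative margin of 0.35 SD, one-sided 0.025, power 0.80 and no true loss. The normal approximation is n ≈ 2(1 − r)(1.96 + 0.84)²/0.35². At r = 0.5 this is 7.84/0.1225 = 64. The exact t calculation gives 67, 41 or 28 completers per arm at r = 0.5, 0.7 or 0.8.

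**Carried-forward values.** A participant with no observation after the reference visit contributes a change of exactly zero. With 3 such participants in 30, a true loss of 0.35 SD appears as 0.35 × 27/30 = 0.315 SD. By simulation, power falls from 0.46 to 0.42 at r = 0.5 and from 0.67 to 0.62 at r = 0.7, compared with 30 complete pairs.

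**The contrast left out.** COMP-MST versus COMP at 6 months, d = 0.70, two-sided 0.05: power is 0.71 with 27 per arm and 0.76 with 30. Before baseline adjustment, the 95% CI half-width with 27 per arm is about 2.007 × √(2/27) = 0.55 SD.

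**The case against.** The strongest reply has five parts.

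- **No decision rule is written.** A reader might infer that the plan counts a non-significant change as maintenance. It does not say so. It says the data will be compared to evaluate "whether or not any significant gains on variables have been maintained over time". A margin or interval criterion may stand in a fuller document. This is right, and the difficulty with a difference test is therefore an inference from the stated comparison.
- **Maintenance is tested elsewhere.** A reader might infer that the maintenance part of the primary aim goes without a randomised test. Hypothesis 1 places maintenance at 3 months, and that visit is in the between-group model. This stands, and it confines the point to 6 months.
- **There is a design reason for stopping at 3 months.** The waitlist is then offered COMP-MST, so a three-arm contrast at 6 months is no longer a clean randomised one. This stands for the waitlist, but not for COMP-MST versus COMP.
- **The 58% is one case.** It rests on r = 0.5, on separate-arm tests and on a between-group effect used as a scale for a within-arm loss. If COMP itself improves, the COMP-MST gain would exceed 0.70 SD and losing half of it would be easier to detect. This stands, so only the range should be read, and only as an illustration.
- **The biases oppose each other.** Selection on significance makes decline more likely to appear, which works against a claim of maintenance. Carrying forward works the other way, and its effect is small at 10% dropout. This also stands: the net direction is unknown, which makes the comparison hard to interpret but does not show that it favours maintenance.

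The opening sentence on between-group differences could be read to cover 6 months. But it names no visit, and the model sentence that follows lists three visits and stops at 3 months.

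**Conclusion.** The point holds for the 6-month conclusion. Followed as written, the plan evaluates 6-month maintenance only through change from an unfixed earlier visit, on outcomes selected for significance, and gives no COMP-MST versus COMP estimate at a visit where both arms are measured and neither is offered a change of treatment. The stated comparison cannot establish maintenance without a margin or interval criterion. Under the assumptions above, a within-arm loss of 0.35 SD would go undetected in 21% to 58% of trials; complete loss of a 0.70 SD gain would almost always be seen. The range rests on an assumed correlation and an assumed loss, because the documents give neither a between-visit correlation nor a within-arm gain. The primary test at post intervention and 3 months is unaffected. This should be changed, but it does not undermine the trial's main analysis.

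**What to change.** - Add 6 months as a level of time in the mixed model, and report the baseline-adjusted COMP-MST minus COMP difference at 6 months with its 95% CI, for all primary and secondary outcomes whether or not they were significant earlier.
- Make no randomised contrast with the waitlist after that group has been offered COMP-MST; describe its later data separately.
- Replace *and/or* with one pre-specified reference visit, post intervention.
- Report the within-group change from that visit to 6 months with a CI, as description, and state how many carried-forward values enter it.

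The cost is a change of wording in the analysis section; the data are already to be collected. The downside is that a claim of maintained gains becomes harder to reach, and with about 27 per arm the 6-month interval will be wide.
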